## 9 ADVERSE EVENTS

Any potential risks and burdens to patients from this study will most likely arise from adverse reactions to the administration of pupil dilatory eye drops (topical mydriasis with tropicamide 1% solution). These are very rare, and attempts will be made to further mitigate against these through the study protocol as outlined below. However, should an adverse event, outcome or reaction come to pass, it will be escalated to the clinical care team as appropriate, documented within patient's clinical notes, the patient's case report form and, with consent and if appropriate a report will be submitted to the Medicines and Healthcare products Regulatory Agency (MHRA) through the British National Formulary (BNF) Yellow Card Scheme.

If this event is perceived to be minor, we will discuss with the patient (including their legal representative, if appropriate) and re-obtain consent to participate. Otherwise, the patient will immediately be withdrawn from the study, and we will seek to obtain consent to retain the participant's data collected up to this point.

1. Adverse events from topical mydriasis will be limited by only applying eye drops to a maximum of one eye per patient.
  - A. Topical mydriasis with tropicamide 1% can rarely cause eye erythema; eye irritation (on prolonged administration); eye pain; headache; hypotension; nausea; syncope.
  - B. Acute closed angle glaucoma. This can occur very rarely following administration of topical mydriasis to dilate pupils. To mitigate this, all patients will be screened for shallow anterior chamber depth using a pen-torch. Such patients will not receive topical mydriasis in this eye on safety grounds.
2. In critically unwell and unconscious patients, pupillary reflexes are used to measure central nervous system (CNS) injury. Dilating the pupil with topical mydriasis prevents this from being measured in the affected eye. Consequently we will take a number of actions to mitigate against the missed diagnosis of CNS injury in participants.
  - A. We will not recruit patients with confirmed or suspected conditions where there is a clinical exclusion for pupillary dilation (e.g. traumatic brain injury, stroke, space occupying lesions (e.g., tumours or encephalitis) or meningitis) or undergoing neurological observation.
  - B. We will ensure topical mydriasis is not applied to one eye and documenting the affected eye, preserving capacity for brainstem monitoring.
  - C. We will use the dilated eye to observe potential signs of neurological injury (e.g., papilloedema), which can be difficult to measure otherwise.

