##### **INCLUSION CRITERIA**

1. At least 16 years old AND
2. Admitted to intensive care (ICU) or high-dependency care units (HDU) AND
3. A requirement for Intensive Care Society Level 2 or 3 care will be eligible to participate(19).

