#### **4.2 EXCLUSION CRITERIA**

Patients may be excluded for any of the following criteria:

1. Patient refusal
2. Next of kin or power of attorney unavailability or refusal
3. Anticipated survival <24 hours
4. Pregnancy
5. Confirmed or suspected conditions where there is a clinical exclusion for pupillary dilation: e.g., traumatic brain injury, meningitis, cerebrovascular accident, space-occupying lesion (tumour, encephalitis etc.).
6. Ophthalmologic conditions: facial trauma precluding visualization of both retinas.
7. Imaging not feasible (equipment/ researcher unavailable or disruptive to care provision).

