## **5 PARTICIPANT SELECTION AND ENROLMENT**

### **5.1 IDENTIFYING PARTICIPANTS**

Patients requiring treatment in intensive care (ICU) or high dependency (HDU) units will be identified and screened for eligibility by members of the clinical care team (medical student, nurses, research nurses and physicians).

Once eligibility has been confirmed, the patient or their legal representative (under Adults with Incapacity (Scotland) 2000 Act) will be approached and information about the study provide in written and verbal form. The initial approach will be made by a member of the clinical care team (embedded medical student, research nurses and physicians) with the agreement of the treating physician.

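### The section 9 bar on recruiting patients under neurological observation is not in the eligibility list, and the related exclusion criterion 5 is only permissive (minor)

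*Protocol*

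**What the plan says.** Section 9, item 2 explains that pupillary reflexes are used to detect central nervous system injury in unconscious patients, and that "Dilating the pupil with topical mydriasis prevents this from being measured in the affected eye". It then introduces its safeguards: "Consequently we will take a number of actions to mitigate against the missed diagnosis of CNS injury in participants". Item 2A is a recruitment rule. It opens "We will not recruit patients with confirmed or suspected conditions where there is a clinical exclusion for pupillary dilation", gives examples in brackets, and ends "space occupying lesions (e.g., tumours or encephalitis) or meningitis) or undergoing neurological observation". Item 2B adds that "We will ensure topical mydriasis is not applied to one eye and documenting the affected eye, preserving capacity for brainstem monitoring".

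The eligibility rules are in section 4. The unnumbered Inclusion Criteria heading has three items: age, admission to intensive or high-dependency care, and level of care ("A requirement for Intensive Care Society Level 2 or 3 care will be eligible to participate"). Section 4.2 lists seven exclusions under a lead-in saying that patients may be excluded for any of them. The one that corresponds to item 2A is criterion 5: "Confirmed or suspected conditions where there is a clinical exclusion for pupillary dilation: e.g., traumatic brain injury, meningitis, cerebrovascular accident, space-occupying lesion". Neurological observation does not appear in it.

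**The concern.** A recruitment bar works only if it is applied when patients are screened. Under section 5.1 screening is done by medical students, nurses, research nurses and physicians, and the patient or representative is approached once eligibility has been confirmed. The schedule in section 6.1 names the screening task as assessment of the eligibility criteria. The bar on patients under neurological observation is not among those criteria; it is in the adverse-events section.

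What is at stake is patient safety and clarity of conduct, not the statistics. A patient whose pupils are being checked could be enrolled and have one pupil dilated, although section 9 says such patients will not be recruited. If that happened, staff would also have two different rules for judging whether the enrolment was a deviation or violation to be reported under section 11.4.

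**Working it through.** The plan gives no figure on this point, so the check is a comparison of texts and a count.

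**Step 1: how many groups does item 2A bar?** In "space occupying lesions (e.g., tumours or encephalitis) or meningitis) or undergoing neurological observation" the bracket closes after meningitis, and neurological observation follows it, joined by *or*. It is therefore a second group and not a further example of the first. Groups barred: 2, both in mandatory terms (will not recruit).

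**Step 2: where does each group appear in section 4?**

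| Group in section 9, item 2A | Force in section 9 | Place in section 4 | Force in section 4 |
|---|---|---|---|
| (a) Confirmed or suspected condition that rules out dilation | Mandatory | 4.2, criterion 5 | Permissive (may be excluded) |
| (b) Under neurological observation | Mandatory | Not named | None |

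**Step 3: count.** Criteria: 3 inclusion + 7 exclusion = 10. Naming neurological observation: 0 of 3 + 0 of 7 = 0 of 10. Groups named in section 4: 1 of 2. Groups carried there with the mandatory force of section 9: 0 of 2.

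**Step 4: does another criterion cover group (b) without naming it?**
- Criterion 5 has an open list of examples, but it is open as to *conditions*. Being under observation is a monitoring status. Item 2A also has an open list of conditions and still adds observation separately; if the open list covered it, the added words would do nothing.
- Criterion 5 includes suspected conditions, so a patient observed because brain injury is suspected is reached. One observed with no confirmed or suspected excluding condition is not.
- Criterion 7 covers imaging that would disrupt care. Dilating a patient whose care includes pupil checks could be judged disruptive, but that is the screener's inference, not a stated rule.

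The mismatch is left with patients under neurological observation who have no confirmed or suspected excluding condition and whose imaging is not judged disruptive. The protocol gives no figure for their number.

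**The case against.** The strongest reply is that nothing here is contradictory. The section 4.2 list is permissive and does not claim to be complete; it nowhere says that a patient under neurological observation should be enrolled. A site can obey sections 4.2 and 9 together, and section 11.2.2 requires staff to be informed about the protocol. A reader might infer that the two sections cannot both be followed; the text does not support that. What stands is narrower: the eligibility list, read alone, admits patients whom section 9 bars.

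A second reply is that the practical risk is close to nil. The approach is made by clinical staff ("embedded medical student, research nurses and physicians) with the agreement of the treating physician"), criteria 5 and 7 will catch many of these patients, and item 2B leaves one eye undilated. This stands as to size. A reader might infer that enrolled patients would lose pupil monitoring altogether; item 2B rules that out. But the physician's agreement is not tied to neurological observation, and none of these safeguards makes the two recruitment rules the same.

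A reader might also infer that the study's own recording of the Glasgow Coma Scale at both visits (section 6.1) would count as neurological observation and so bar everyone. Nothing in the protocol suggests this: the score is one item in a row of routine pre-sample observations. No special definition is needed on that account.

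**Conclusion.** The point holds and is minor. Section 9 bars two groups outright; section 4.2 carries one of them only permissively and does not name the other (0 of 10 criteria). The result is a safety rule placed where a screener may not apply it, not a contradiction and not a demonstrated harm. No endpoint, analysis or sample-size statement depends on it.

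The conclusion rests on two readings. The first is that the phrase after the closing bracket in item 2A is a separate group, which the punctuation and the *or* support. The second is that screeners work mainly from the eligibility list, which sections 5.1 and 6.1 imply but do not state. If every screener also applies section 9, no ineligible patient is enrolled and the change is only one of consistency. How many patients are affected cannot be estimated from the protocol.

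**What to change.** Reword criterion 5 in section 4.2. Keep its present description and examples of conditions that rule out dilation, then add after them: *or under neurological observation; nobody in either group will be recruited (see section 9, item 2A)*. The words *in either group* matter. Without them the mandatory statement could be read as covering only the added patients, leaving brain injury and stroke under the permissive lead-in. The lead-in and the other six exclusion criteria can stay as they are.

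The cost is a small protocol amendment, which under section 11.3 needs review by the Chief Investigator, sponsor authorisation, and ethics committee and local R&D approval before anyone is enrolled under it. Assessments and analyses do not change. Measured against section 9, no further eligible patients are lost. Measured against section 4.2 read alone, some would be, by a number the protocol does not allow one to state.

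### Section 9 item 2B relies on the undilated eye for brainstem monitoring but never requires that eye's pupil to be assessable before the other eye is dilated

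*Protocol*

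**What the plan says.** Protocol section 9, item 2, explains that pupillary reflexes are used to detect central nervous system injury in critically unwell and unconscious patients, and that "Dilating the pupil with topical mydriasis prevents this from being measured in the affected eye". Three actions follow against a missed diagnosis.

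- **2A**, at recruitment: "We will not recruit patients with confirmed or suspected conditions where there is a clinical exclusion for pupillary dilation". It also keeps out patients under neurological observation.
- **2B**, at imaging: "We will ensure topical mydriasis is not applied to one eye and documenting the affected eye, preserving capacity for brainstem monitoring".
- **2C**, at imaging: "We will use the dilated eye to observe potential signs of neurological injury", with papilloedema as the example.

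Item 1 of the same section limits exposure by "only applying eye drops to a maximum of one eye per patient". Item 1B adds that "all patients will be screened for shallow anterior chamber depth using a pen-torch", with the consequence "Such patients will not receive topical mydriasis in this eye on safety grounds".

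On eligibility, section 4.2 has one eye-specific criterion (number 6): "Ophthalmologic conditions: facial trauma precluding visualization of both retinas". The schedule in section 6.1 collects ophthalmologic comorbidities at baseline. At both scans it records which eye was dilated.

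**The concern.** Item 2B says where drops must not go. It sets no condition on whether the eye left alone can do the job assigned to it. If that eye cannot be opened, is absent, or has a pupil that does not react, leaving it undilated preserves nothing.

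At stake is a stated safeguard for patients who may be unconscious. Item 2A acts when patients are recruited, so it cannot cover a neurological event that begins after enrolment. Item 2C looks at the back of the dilated eye and is not a test of the pupillary reflex. After enrolment, item 2B is the only one of the three actions that keeps a pupillary reflex available.

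**Working it through.** The protocol states no figure on this point, so there is none to reproduce. The check is whether any rule makes the giving of drops, or the choice of eye, depend on the other pupil.

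**Rules that might close the gap**

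| Place in the protocol | What it does | Does it check the undilated pupil? |
|---|---|---|
| Section 9, item 1 | Caps drops at one eye | No |
| Section 9, item 1B | Pen-torch screen of chamber depth; a shallow eye gets no drops | No |
| Section 9, item 2A; section 4.2, criterion 5 | Keep out known or suspected conditions that rule out dilation, at recruitment | No |
| Section 9, item 2C | Looks for signs such as papilloedema in the dilated eye | No |
| Section 4.2, criterion 6 | Concerns facial trauma that prevents the retinas being seen | No |
| Section 5.1 | Treating physician agrees to the approach to the patient | No |
| Section 6.1 | Records eye comorbidities at baseline, and the eye dilated at each scan; lists no pupil size or reactivity | No |
| Section 7 | Trains the OCT operator to run the device | No |

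**How the gap can be reached**

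1. *Through item 1B.* If one eye has a shallow chamber, only the other eye may be dilated. No rule then asks whether the barred eye's pupil reacts.
2. *Through criterion 6.* On its natural reading, exclusion applies only when neither retina can be seen. A facial-trauma patient with one eye that can be imaged is then eligible, and that is the eye that would be dilated.
3. *Through other eye disease.* Criterion 6 covers facial trauma only. Any other long-standing problem in the undilated eye is recorded as a comorbidity and does not bar drops. This route does not depend on how criterion 6 is read.

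**Count**

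Testable pupils while the drops act = assessable pupils - 1 dilated.

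- Two assessable pupils: 2 - 1 = 1. Item 2B works as intended.
- One assessable pupil, and that eye dilated: 1 - 1 = 0. Item 2B preserves nothing.

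The schedule in section 6.1 has a baseline scan and a repeat after 12-72 hours, so the situation can arise at up to 2 scans per patient. Of the 3 listed actions, 1 acts at recruitment (2A) and 2 act afterwards (2B and 2C). Only 1 (2B) keeps a pupillary reflex test.

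The protocol gives neither the frequency of an unassessable pupil nor the duration of the drops' effect. No probability of harm is calculated.

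**The case against.** The strongest reply is that item 2B states its own purpose. Dilating a patient's only usable pupil would defeat that purpose, so a careful operator would not do it, and what is missing is only an obvious bedside step. Several other points support this.

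- An unexplained fixed pupil would itself raise suspicion of a neurological condition, and so lead to exclusion under criterion 5 or item 2A. Facial trauma severe enough to close the lids may do the same through suspected brain injury.
- Criterion 6 can be read as requiring both retinas to be visible, which would exclude the one-eyed facial-trauma case.
- Criterion 7 in section 4.2 allows exclusion when imaging would disrupt care.
- Section 7 puts data collection under the chief investigator's supervision, by staff qualified by training, experience and GCP certification.
- Section 6.1 records changes in status and the Glasgow Coma Scale at both scans.
- The item 1B route needs a second, separate defect in the barred eye. If both eyes are examined, the pen-torch would reveal closed lids or a missing eye.
- Drops are capped at one eye and not mandated. Harm also requires a new neurological event while they act.

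Most of this stands as a limit on size: the affected group is small. None of it is a check on the other pupil. Criterion 5 and item 2A act at recruitment. Criterion 7 is a discretion that does not mention pupils. Status and coma score do not test the reflex. A chamber-depth screen that happens to reveal a closed eye has no written consequence for drops in the other eye. The inference from item 2B's purpose is reasonable, but the protocol undertakes to ensure this protection and should not leave it to inference.

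**Conclusion.** The concern holds. Staff can follow every written procedural step and leave a patient with no testable pupil while the drops act, in which case the protection claimed in item 2B fails. This is limited to patients with one assessable pupil who are given drops in that eye. The group is small and cannot be sized from the protocol. No endpoint, estimate or analysis changes.

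The conclusion rests on two things: the absence of any rule linking drops to the other pupil, and the protocol's own statement that the reflex is lost in a dilated eye. It does not rest on a particular reading of criterion 6. It is a minor design point, worth acting on because the remedy costs almost nothing.

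**What to change.** Add one sentence to section 9, item 2B: at each scan, drops are given only after a pen-torch check confirms that the eye to be left undilated can be opened and has a reactive pupil; otherwise the patient is imaged without drops or not imaged.

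The check can be done together with the chamber screen that item 1B already requires, so it needs no new equipment and adds a few seconds. The downside is that a rare patient is imaged undilated, possibly with poorer image quality, or is not imaged. Section 8.2 already provides for removing unsatisfactory images.

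As a separate and optional clarification, criterion 6 in section 4.2 could state whether one eye that can be imaged is enough for eligibility. That tidies the wording but does not replace the check.

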## 10 OVERSIGHT ARRANGEMENTS

### 10.1 INSPECTION OF RECORDS

Investigators and institutions involved in the study will permit trial related monitoring and audits on behalf of the sponsor, REC review, and regulatory inspection(s). In the event of audit or monitoring, the Investigator agrees to allow the representatives of the sponsor direct access to all study records and source documentation. In the event of regulatory inspection, the Investigator agrees to allow inspectors direct access to all study records and source documentation.

## **10.2 STUDY MONITORING AND AUDIT**

The ACCORD Sponsor Representative will assess the study to determine if an independent risk assessment is required. If required, the independent risk assessment will be carried out by the ACCORD Quality Assurance Group to determine if an audit should be performed before/during/after the study and, if so, at what frequency.

Risk assessment, if required, will determine if audit by the ACCORD QA group is required. Should audit be required, details will be captured in an audit plan. Audit of Investigator sites, study management activities and study collaborative units, facilities and 3rd parties may be performed.

## **11 GOOD CLINICAL PRACTICE**

### **11.1 ETHICAL CONDUCT**

The study will be conducted in accordance with the principles of the International Conference on Harmonisation Tripartite Guideline for Good Clinical Practice (ICH GCP).

Before the study can commence, all required approvals will be obtained and any conditions of approvals will be met.

### **11.2 INVESTIGATOR RESPONSIBILITIES**

The Investigator is responsible for the overall conduct of the study at the site and compliance with the protocol and any protocol amendments. In accordance with the principles of ICH GCP, the following areas listed in this section are also the responsibility of the Investigator. Responsibilities may be delegated to an appropriate member of study site staff.

#### **11.2.1 Informed Consent**

The Investigator is responsible for ensuring informed consent is obtained before any protocol specific procedures are carried out. The decision of a participant to participate in clinical research is voluntary and should be based on a clear understanding of what is involved.

Participants must receive adequate oral and written information – appropriate Participant Information and Informed Consent Forms will be provided. The oral explanation to the participant will be performed by the Investigator or qualified delegated person and must cover all the elements specified in the Participant Information Sheet and Consent Form.

The participant must be given every opportunity to clarify any points they do not understand and, if necessary, ask for more information. The participant must be given sufficient time to consider the information provided. It should be emphasised that the participant may withdraw their consent to participate at any time without loss of benefits to which they otherwise would be entitled.

The participant will be informed and agree to their medical records being inspected by regulatory authorities and representatives of the sponsor(s).

The Investigator or delegated member of the trial team and the participant will sign and date the Informed Consent Form(s) to confirm that consent has been obtained. The participant will receive a copy of this document and a copy filed in the Investigator Site File (ISF) and participant's medical notes (if applicable).

#### **11.2.2 Study Site Staff**

The Investigator must be familiar with the protocol and the study requirements. It is the Investigator's responsibility to ensure that all staff assisting with the study are adequately informed about the protocol and their trial related duties.

### **11.2.3 Data Recording**

The Principal Investigator is responsible for the quality of the data recorded in the CRF at each Investigator Site.

